### Data monitoring

There will be no data monitoring committee, interim analyses, or auditing for the study as it evaluates behavioural interventions that are currently being offered. Should a participant experience any adverse events or other unintended effects, these will be recorded by the clinicians and CBR and managed following regular procedures. Any scores that are considered critical or at-risk, particularly for the CES-D and BAI, will warrant a follow-up discussion and recommendation for the mother to seek further services. The CBRs may suggest that the participant contact their healthcare provider and provide a list of mental health resources if needed.

### Ethics and dissemination

Ethics approval has been obtained from the University of Ottawa Research Ethics Board (REB # H-02-23-8940) and all participants will provide written consent to participate in the research, to be contacted for follow-ups, and for researchers to access their clinical files. Participation in the research is voluntary and mothers will be able to receive services at BTC or MWCHC regardless of their desire to participate. Mothers at BTC and MWCHC will be made aware that they are under no obligation to participate and that if they choose to participate, they are able to withdraw from the study at any time and refuse to answer any questions without suffering any consequence. They will also have the option to take breaks while answering the questionnaires and will be provided with a list of current resources in their area should they experience any distress. BTC and MWCHC clinicians will be available to debrief with participants and support them as needed. In appreciation for their time and efforts, mothers will receive food vouchers for $50 at baseline, $75 at 12 months, and $100 at 24 months. The amounts increase to reflect the increased value of additional data points, to compensate for challenges that mothers may have in maintaining contact with the research group, and to reduce attrition. Mothers who are no longer engaged in services but participate in the research will also receive the compensation.

The results of the study will be communicated and disseminated within scientific and clinical services communities. Dissemination outputs will include fact sheets, research briefs, research conference poster and oral presentations, as well as scientific articles submitted to international peer-reviewed journals. The authors will consist of members of the research team who have made significant contributions to the study design, data collection and analysis, and manuscript writing. Participants’ identities will not be revealed in any publications resulting from this study.

## Discussion

This study is the first to examine the effectiveness of infant mental health components of a mother-child relationship-focused intervention program on infant mental health outcomes as compared to a mother-focused program. It aims to establish the comparative effectiveness and mechanisms of change of the infant mental health components of BTC, as well as estimate the long-term SROI of the integrated BTC approach. The involvement of MWCHC participants as a control group is a considerable strength of the study, thus making it possible to attribute changes in infant mental health outcomes to the enhanced BTC intervention. Although non-randomized studies suffer from an inherent selection bias, randomization is not possible due to feasibility and ethical reasons. Analytic approaches will be used to minimize any baseline differences between the BTC and MWCHC groups.

It is important to note that while the MWCHC program does not provide the same level of direct intervention with children as the BTC program, children do receive healthcare and well-baby visits. As well, MWCHC mothers receive basic parenting supports and mental health and addiction services that indirectly benefit their children. Their participation in this study will allow them to receive a summary report after every time point, containing an overview of their results as well as a developmental report for their child that they would not have otherwise received. Among other benefits for MWCHC participants, the implementation of the clinical measures will allow for better screening and referral and will increase evidence-based knowledge provided to clinicians. The introduction and embedment of a CBR will also enhance the capacity for research at each site, thus increasing the quality of regular clinical services being offered.

With over 25 years of developing infant mental health programming, BTC is in a unique position to study the effectiveness of an infant mental intervention for children of substance-involved mothers. Canada lags behind other wealthy nations with regards to investments, policies, and practices that support early child mental health [19]. ACEs in infancy and early childhood set the stage for lifelong mental health difficulties, with a failure to intervene resulting in significant health and economic consequences [18]. In the aftermath of the COVID-19 pandemic, there is an urgent need to prioritize the mental health of the next generation. Bringing together a nationally acclaimed team, this study aligns with national strategies to establish strong evidence for infant mental health interventions that reduce exposure to ACEs and support the mother-child relationship.

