**Methods:**

One hundred substance-involved pregnant and/or parenting women with children between the ages of 0–6 years old will be recruited through the Breaking the Cycle and Maxxine Wright intervention programs, in Toronto, Ontario, Canada and Surrey, British Columbia, Canada, respectively. Children’s socioemotional development and exposure to risk and protective factors, mothers’ mental health and history of ACEs, and mother-child relationship quality will be assessed in both intervention programs. Assessments will occur at three time points: pre-intervention, 12-, and 24-months after engagement in the intervention program.

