## Methods

### Design

This intervention study is designed as a non-randomized, non-equivalent, comparison study with two equally allocated parallel groups: the BTC intervention group and the MWCHC intervention group. Given that the two intervention programs serve a similar demographic of women, researchers will compare the BTC and MWCHC groups to establish the comparative effectiveness and mechanisms of change of the additional infant mental health component of BTC. The study has been approved by the University of Ottawa Research Ethics Board (REB # H-02-23-8940) and is registered with ClinicalTrials.gov (NCT05768815). All research is performed in accordance with relevant guidelines and regulations. This protocol paper adheres to the SPIRIT guidelines (see Additional file 1).

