### Participants

Participants will comprise substance-involved pregnant and/or parenting women with children between the ages of 0–6 years old. We aim to recruit a total of 100 participants: 50 through the BTC intervention and 50 through the MWCHC intervention. To be eligible for the study, participants must: be receiving services at either BTC or MWCHC; have a child under the age of 6 years; and be able to complete the study questionnaires in English. There are no exclusion criteria for participation in this study.

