#### Maxxine Wright

Founded in 2005 and located in Surrey, British Columbia, the MWCHC supports substance-involved women who are pregnant and/or have young children. Women do not need to have children in their care to receive services. MWCHC is a partnership between the Fraser Health Authority, Atira Women’s Resource Society, and the BC Ministry for Children and Family Development. MWCHC addresses maternal substance use and exposure to violence through a multidisciplinary approach. This includes the following philosophical/theoretical approaches: supportive and woman-centered (i.e., creating a safe and supportive environment for women), harm reduction (i.e., recognizing recovery as a long process and a stepping stone toward wellness), trauma-informed (i.e., recognizing that many women have experienced serious trauma), multidisciplinary and wraparound (i.e., providing wraparound health care and social support services to address women’s and children’s needs), health-centered (i.e., providing health care expertise and positive experiences for women and their infants/children), and relational (i.e., focusing on respectful, non-judgmental relationships and compassion) [36]. Primary services offered include addiction counselling, primary health care, and opiod agonist therapy. Within MWCHC, child-focused services are limited to primary health care (e.g., well baby checks, immunizations, referrals for developmental services, growth tracking, and childcare) and do not address the mother-child relationship.

Both the BTC and MWCHC intervention programs are considered integrated maternal substance-use programs in that they offer supports in additional to maternal substance use treatment [36]. Both programs provide services to mothers and their children. For example, both intervention programs have access to childcare, instrumental parenting support, and developmental education. The main difference between the two intervention programs is that BTC uses an infant mental health framework and provides therapeutic supports (e.g., home visitations) to support child development and the parent-child relationship. Given that MWCHC serves a similar demographic of women as BTC but does not focus on infant mental health, they will serve as a comparison site. Table 1 below presents an overview of the services offered by BTC and MWCHC.

**Table 1 Tab1:** Comparison of services between Breaking the Cycle (BTC) and Maxxine Wright Community Health Centre (MWCHC)

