Service feature		Service approach	BTC	MWCHC
Target population	Pregnant or parenting women with substance use difficulties	Mother-focused	Yes (0-6 years)	Yes (0-6 years)
Structure	Ongoing relationship with the child	Mother-focused	Yes	Yes
	Plan to parent	Infant Mental Health	Yes	No
	Comprehensive, wrap-around approach	Mother-focused	Yes	Yes
	Women-centered, trauma-informed	Mother-focused	Yes	Yes
	Infant Mental Health Frameworks	Infant Mental Health	Yes	No
Basic needs support	Food, clothing, transportation	Mother-focused	Yes	Yes
	Childcare	Mother-focused	Yes	Yes
Broader Services	Individual Family Advocacy	Mother-focused	Yes	Yes
	Case Management/Service Coordination	Mother-focused	Yes	Yes
	Primary Health Care Services (mother/child)	Mother-focused	Yes	Yes
Addiction Services	Individual Addictions Services	Mother-focused	Yes	Yes
	Relapse Prevention Group	Mother-focused	Yes	Yes
	Recovery Support Group	Mother-focused	Yes	Yes
	Trauma and Interpersonal Violence Group	Mother-focused	Yes	Yes
Mental Health	Individual Mental Health Counselling	Mother-focused	Yes	Yes
	Individual Trauma Counselling	Mother-focused	Yes	Yes
	Life Skills/Emotion Coping Group	Mother-focused	Yes	Yes
Prenatal Services	Pregnancy Outreach Program	Mother-focused	Yes	Yes
	Prenatal care Services	Mother-focused	Yes	Yes
Instrumental Parenting Support	Basic Parenting support, child management, developmental education	Mother-focused	Yes	Yes
Child Development Supports	Annual Developmental Assessments	Infant Mental Health	Yes	No
	Developmental Screening (annual)	Infant Mental Health	Yes	Yes
	Individualized Developmental Therapy Plan	Infant Mental Health	Yes	No
	Home-visitation focused on child development	Infant Mental Health	Yes	No
	Therapeutic childcare	Infant Mental Health	Yes	No
Mother-child Relationship Support	Individual parenting support/Interaction Guidance	Infant Mental Health	Yes	No
	New Mom’s Support Group (Infant 0-6 months)	Infant Mental Health	Yes	No
	Parent-Child Mother Goose Program	Infant Mental Health	Yes	No
	Learning through Play Group (infant: 6+months)	Infant Mental Health	Yes	No
	Cooking Healthy Together Group	Infant Mental Health	Yes	No
	Parenting Group Support	Infant Mental Health	Yes	Yes

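### With one site per programme and care status not equalised, the design cannot support attributing outcome differences to BTC

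*Protocol article*

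**What the plan says.** The Design section describes a "non-randomized, non-equivalent, comparison study with two equally allocated parallel groups". According to the Abstract (Methods), mothers are "recruited through the Breaking the Cycle and Maxxine Wright intervention programs, in Toronto, Ontario, Canada and Surrey, British Columbia, Canada, respectively". The Maxxine Wright section explains that, because MWCHC serves a similar demographic but "does not focus on infant mental health, they will serve as a comparison site". Each programme is therefore represented by one centre, and Data collection places one community-based researcher (CBR) at each.

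On who the programmes serve, the Maxxine Wright section says of MWCHC: "Women do not need to have children in their care to receive services". Table 1, under Structure, lists "Plan to parent" as Yes for BTC and No for MWCHC. The Participants section describes pregnant and/or parenting women. Its criteria are receipt of services at either programme, a child under 6 and the ability to complete the questionnaires in English. It adds: "There are no exclusion criteria for participation in this study".

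Statistical analysis compares the groups' slopes in a linear mixed model, adjusting for demographic variables. The examples given are maternal age, socioeconomic status and maternal ACEs. The Discussion then says that the control group is a strength, "thus making it possible to attribute changes in infant mental health outcomes to the enhanced BTC intervention". The sentences that follow concede selection bias in general terms and promise analytic handling of baseline differences.

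**The concern.** The attribution sentence claims a property that the design does not have. With one site per arm, whatever makes children in Toronto change differently from children in Surrey is indistinguishable from an effect of the infant mental health component. Local child services, staffing and referral patterns are examples. The concession that follows concerns selection bias. It does not mention that site and programme are the same variable, and adjustment for measured maternal characteristics cannot undo that.

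Care status adds a second route. A mother without the child in her care can receive services at MWCHC, and nothing in the study criteria makes the two groups comparable in this respect. ASQ-3 and ASQ-SE-2 are both completed by the mother, so care status could plausibly affect both the child's course and what the mother can report.

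The consequence reaches beyond question 1a. The SROI in question 3 is built on the comparative evidence from question 1, so a site or selection difference would pass into a stated return per dollar invested in BTC.

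**Working it through.** **1. Does the plan's own figure reproduce?** Inputs from Sample size and power calculations: d = 0.70, two-sided alpha 0.05, 34 completers per group, about 30% attrition.
- Noncentrality = 0.70 × √(34/2) = 2.89 with 66 df. Noncentral t power = 81.2%, against 81.1% stated.
- 34 / 0.70 = 48.6, rounded up to 49 per group, so N = 98, as stated.

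The arithmetic is sound. It treats mothers as independent and allows no site effect.

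**2. Can site be separated from programme?** Sites per arm: 1 and 1. Degrees of freedom for between-site variance within arm: (1 − 1) + (1 − 1) = 0. A site term and a programme term would be the same column of the model. Adding mothers at the same two sites leaves this unchanged, so no corrected sample size exists.

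**3. How much could a site effect matter?** The documents give no intraclass correlation (ICC), so the values below are assumptions. With total variance 1 and n per site, the usual test uses a variance per mean of (1 − ICC)/n, whereas the true variance is ICC + (1 − ICC)/n. The test statistic is inflated by the square root of 1 + n × ICC/(1 − ICC). The real two-sided error is 2 × P(t > t₀.₉₇₅ / inflation).

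| Assumed ICC of change | Variance ratio, n = 34 | Type I error, n = 34 | Type I error, n = 50 |
|---|---|---|---|
| 0.01 | 1.34 | 9.0% | 10.9% |
| 0.02 | 1.69 | 13.0% | 16.6% |
| 0.05 | 2.79 | 23.6% | 30.0% |

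The error grows with n because the site component does not shrink. These figures treat sites as draws from a wider population, so they concern inference beyond Toronto and Surrey.

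**4. The same point without a random site effect.** Suppose there is no programme effect, but site or selection shifts mean change by b SD (assumed). Noncentrality is b × √17, and at 34 per group the test is significant with these probabilities:
- b = 0.2 (0.82): 12.8%
- b = 0.3 (1.24): 23.0%
- b = 0.5 (2.06): 52.9%

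**5. Care status.** The MWCHC section states that the child need not be in the mother's care. The Participants criteria contain no care-status condition, and the covariate examples do not include it. The document therefore states a possible difference between the groups and shows no step that equalises it.

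**The case against.** Several points on the other side are fair.
- **Disclosure.** The design is openly labelled non-randomized and non-equivalent, selection bias is conceded, and the covariates are given only as examples, so the full list may sit in an analysis plan. This stands for measured baseline differences. It does not reach the aliasing of site with programme, which is nowhere named and which no covariate list can resolve.
- **Slopes, not levels.** Comparing change removes stable differences in level between sites. That stands, and only site differences in change remain. Those are the differences at issue in question 1a.
- **Entry rules.** A reader might infer from Table 1 that BTC requires a plan to parent, and so that mothers not caring for the child can enter only the comparator arm. The documents do not support this. The row sits under Structure, is tagged as an infant mental health feature and is never stated as an admission rule. The row above it, on a continuing relationship with the child, is Yes at both sites. Participants are also described as pregnant and/or parenting women. What stands is narrower: MWCHC's service condition is explicit, and eligibility does not equalise care status.
- **Rater.** One might infer that rater is confounded with arm for the primary outcomes through the site-based researcher. It is not, because mothers complete the ASQ-3 and ASQ-SE-2. Rater coincides with arm for the CBR-coded MBQS, a secondary measure.
- **Missing data.** It is tempting to say that MWCHC will have more missing or less informed outcome data. That is plausible, but nothing in the documents establishes or quantifies it.

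**Conclusion.** The statement that the control group allows changes to be attributed to BTC is not supported. The aliasing of programme with site is a matter of fact from the design description and needs no assumption. The care-status point rests on one explicit sentence about MWCHC and on the absence of any care-status criterion in the study's eligibility. It shows that a difference is possible, not that one exists.

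The size is illustrative only. With an assumed 1% to 5% of the variance in change between sites, type I error at 34 per group would be about 9% to 24% for inference beyond these two sites. A reader might conclude that the planned 5% test is therefore wrong in itself. That goes too far. These error rates do not apply to a comparison of the two programmes as delivered at their own sites, and the stated power and sample size reproduce. What fails is the causal reading of that comparison. The study can proceed, but the sentence should not stand as written.

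**What to change.** 1. **Reword the attribution sentence in the Discussion**, for example: *the study estimates differences between the two programmes as delivered at their sites; site and selection effects cannot be separated.* Name the one-site-per-arm aliasing as a limitation, including the rater for the MBQS. This costs only text.
2. **Carry the limitation into the SROI**, stating that the question 1 evidence it uses includes any site or selection difference. This also costs only text.
3. **Record at baseline whether the index child is in the mother's care.** Clinical file review is already planned, so this adds one data item. Women still pregnant at enrolment need their own category.
4. **Repeat the 1a analysis as a sensitivity analysis**, either adjusted for care status or restricted to mothers with the child in their care. The restricted analysis has fewer mothers and less precision, and neither version removes the site aliasing.

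Care status should not become a new entry rule on the strength of this point. A rule that required the index child to be born would exclude women still pregnant with that child, who are in the target population. A rule based on planning to parent would select on something that Table 1 lists as part of BTC's infant mental health approach.

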## Data Availability

Not applicable.

## Abbreviations

ACEs: Adverse Childhood Experiences
BTC: Breaking the Cycle
CBR: Community-based researcher
MWCHC: Maxxine Wright Community Health Centre
SROI: Social return on investment
